### Outcome

1.1.

•Improved data use in decision-making among health management staff in districts through the DIPH strategy.•Improved utilization level of maternal health services (antenatal care, delivery, postnatal care, and FP services) in districts through the DIPH strategy.

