### Determination of sample size

2.5.

The sample size estimation for the required number of woredas per study arm is based on the statistical formula recommended by Hayes and Bennett (29), assuming 80% power and at least 25 percentage point difference in the performance of data use and maternal healthcare services.$$c=1+(z_{\alpha /2}+z_{\beta }{)}^{2}\frac{\pi_{0}(1-\pi_{0})/m+\pi_{1}(1-\pi_{1})/m+(k_{0}^{2}\pi_{0}^{2}+k_{1}^{2}\pi_{1}^{2})}{{\left(\pi_{0}-\pi_{1}\right)}^{2}}$$where *C* is the number of clusters required (woredas), *Z_α_*_/2_ is the confidence level (95%), Z*_β_* is required power (80%), π_0_ is the true proportion in the absence of intervention (50%), π_1_ is the true proportion in the presence of intervention (75%), *m* implies the individuals sampled in each cluster/woreda (10), *k*_0_ is the coefficient–variation of true proportion in the absence of intervention (0.096942), and *k*_1_ is the coefficient–variation of true proportion in the presence of intervention (0.096942).

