#### Preparatory phase

2.8.2.

*Prepare materials***.** Logistics, including job aids such as guidelines, has been prepared before the implementation.

*Organizing the DIPH field team*. The researcher team, also referred to as the implementation support team, has consisted of six members, including one health professional each from health service management, health informatics, reproductive health, epidemiology, and biostatistics and one health management staff from the zonal health department as a coordinator, supervisor, and data manager. To facilitate the overall activities, the principal investigator of the research is responsible. The field team has the following roles: prepare and develop data collection tools, provide training to health professionals, and conduct monthly supportive supervision using a performance checklist in line with the health facility PRT. The teams will acquire and examine data from six district health offices, which are DIPH-implementing districts, and six control districts that will not be participating in DIPH. According to the priority areas determined by the district health offices, the PRT evaluates monthly progress toward a set of indicators.

The assistance provided by the DIPH team, which consists of action plan preparation, follow-up, and supportive supervision, benefits the team leaders of the district health office. As the purpose of the DIPH is to strengthen decision-making, unit leaders of district health offices are working with the DIPH field team to gain a clearer understanding of their data and make better use of it.

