### Operational definition

2.9.

**The DIPH approach** is a structured decision-support approach in promoting the use of locally available data for health decision-making at the woreda level (7).

**Data use in decision-making** is a process through which district health managers, decision-makers, and stakeholders explicitly consider the information in gap identification, prioritization, root cause analysis, action plan development, and follow-up. The five components of the outcome variable were identifying indicators in the department, calculating targets vs. achievements, providing feedback to health workers at the lower levels, calculating program coverage, and evidence showing the use of data to notify decisions. It has been measured by computing 20 yes/no questions and said to be good if all the responses are yes unless poor (30, 31).

**Maternal health service utilization** is the overall utilization of common maternal healthcare services such as antenatal care, delivery, postnatal care, and family planning from a provider standpoint (report) in percent. It has been measured using 10 core indicators, each at 100% (21, 32).

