### Data collection tools and procedures

2.10.

A pre-tested interviewer-administered structured questionnaire, based on the Performance of Routine Information System Management tools (version 3) (30) and adapted to the local context, has been used to improve data use in decision-making and utilization of maternal healthcare services through the DIPH approach in districts of the Gedeo Zone, southern Ethiopia, 2022. The questionnaire has two broad categories, namely, data use in decision-making and utilization of maternal healthcare service. It will be organized in an English version and then translated into local languages (Gedeuffa and Amharic) and finally retranslated into an English version to ensure consistency. The collection of baseline data has been carried out by the organized field teams. For end-line survey data collection, an independent team of four data collectors and one supervisor has been recruited for 1 month.

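### Maternal service utilisation is a reported district percentage but is sized as a yes/no proportion among 10 staff per woreda, so its 6 woredas per arm and 80% power are unsupported

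*Protocol article*

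**What the plan says.** All references are to the protocol article.

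- **Outcome (1.1)** claims the effect at district level: "Improved utilization level of maternal health services (antenatal care, delivery, postnatal care, and FP services) in districts through the DIPH strategy".
- **Operational definition (2.9)** makes the outcome a percentage "from a provider standpoint (report) in percent. It has been measured using 10 core indicators, each at 100"%. The only rule that turns answers into a yes/no result belongs to the other outcome, data use: "It has been measured by computing 20 yes/no questions and said to be good if all the responses are yes unless poor".
- **Determination of sample size (2.5)** covers both outcomes in one calculation, "assuming 80% power and at least 25 percentage point difference in the performance of data use and maternal healthcare services", using a two-proportion cluster formula in which m is the "individuals sampled in each cluster/woreda (10"). The table gives the two outcomes identical rows: 50% at baseline, 25% increase, 10 staff per woreda, 6 woredas per arm. The total is 120 staff.
- **Data collection tools and procedures (2.10)**: "The questionnaire has two broad categories, namely, data use in decision-making and utilization of maternal healthcare service". The response format of the maternal section is not stated.
- **Preparatory phase (2.8.2)**: "The teams will acquire and examine data from six district health offices" that implement DIPH, and from six control districts.
- **Data management (2.12)** names χ² tests, t-tests and difference-in-differences for both outcomes together, without stating the unit of analysis for either.

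**The concern.** A reported coverage percentage is a property of a woreda's services, not of an individual manager. Ten colleagues describing their own office's figure do not give ten independent observations of it, and no rule converts the figure into a 0/1 result per person. The variance π(1−π)/m with m = 10 staff therefore describes a quantity that this outcome does not have.

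Two things are at stake. One of the two effectiveness outcomes has no valid size or power statement. And if the analysis follows the sizing and treats staff records as the sample, a t-test can declare an effect far more often than 5% of the time when there is none. The dissemination section ties scale-up to demonstrated effectiveness, so a false positive would have consequences.

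**Working it through.** **Inputs from section 2.5 and its table.** π₀ = 0.50, π₁ = 0.75, m = 10, k₀ = k₁ = 0.096942, 80% power, two-sided 5% (the formula uses z for α/2), so (1.960 + 0.842)² = 7.849.

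**Step 1: the plan's own figure.** c = 1 + 7.849 × [π₀(1−π₀)/m + π₁(1−π₁)/m + k²(π₀² + π₁²)] / (π₁ − π₀)²

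- Binomial part: (0.25 + 0.1875)/10 = 0.04375
- Between-woreda part: 0.096942² × (0.25 + 0.5625) = 0.00764
- Sum: 0.05139; denominator: 0.25² = 0.0625
- c = 1 + 7.849 × 0.05139/0.0625 = 7.45, which is 8 woredas per arm (160 staff), not 6 (120)

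With 6 per arm the printed formula gives power Φ(√(5 × 0.0625/0.05139) − 1.960) = Φ(0.506) = 69%. So the stated figure is not reproduced even for a genuine yes/no outcome. That is a separate matter, which also affects data use.

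**Step 2: how much of the formula does not apply.** 0.04375/0.05139 = 85% of the variance numerator is the binomial term. Without it, at the printed k, c = 1 + 7.849 × 0.00764/0.0625 = 1.96.

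**Step 3: power with one value per woreda.** Two-sided unmatched t-test, 6 versus 6, 10 df, difference 25 points, noncentrality 25/(SD × √(2/6)). The printed k implies an SD of 0.096942 × 50 = 4.8 points in control and 0.096942 × 75 = 7.3 points under intervention, about 6.2 pooled. The other SDs are assumptions.

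| Between-woreda SD (points) | Noncentrality | Power |
|---|---|---|
| 6.2 (from printed k) | 7.0 | >99% |
| 10 | 4.33 | 97% |
| 15 | 2.89 | 74% |
| 20 | 2.17 | 50% |
| 25 | 1.73 | 35% |

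Power reaches 80% only if the SD is about 13.9 points or less.

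**Step 4: type I error if staff records are the unit.** Simulation under no effect: 6 pairs of woredas, 10 staff each, ordinary t-test on 60 versus 60 records at end line. Reporting noise within an office is expressed relative to the between-woreda SD. The within-pair correlations are assumptions.

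| Within-pair correlation | Identical answers | Noise SD = between-woreda SD |
|---|---|---|
| 0 (matching ineffective) | 58% | 42% |
| 0.5 | 44% | 28% |
| 0.7 | 32% | 19% |
| 0.9 | 12% | 7% |

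**The case against.** **The unit of analysis is not stated.** Section 2.12 does not say that the maternal outcome is tested on staff records. Section 2.6 treats woredas as clusters, section 2.8.2 has the team obtaining district-office data, and a t-test on woreda percentages would fit the wording. This stands: the type I error figures are conditional. The total of 120 staff and the questionnaire section point towards staff records but do not fix them. Likewise, one value per woreda is the natural reading, not a stated fact.

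**The document does give a variability figure.** The printed k is part of a calculation stated to cover both outcomes, and at that k a woreda-level comparison has more than 99% power. On the plan's own inputs the wrong formula is conservative for this outcome. This also stands, with the qualification that k has no source and is shared unchanged by two quite different outcomes.

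**Allocation is matched.** Section 2.6 matches woredas on performance and distance, which lowers false positives. In Step 4 the excess shrinks as pair correlation rises, but it remains at every value tried.

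**The 10-df power figures are for an unmatched end-line comparison.** A paired, baseline-adjusted analysis of six pairs leaves about 4 df. At SD 15 points, 74% would become about 59% with no pair correlation, or about 86% at 0.5. The table is therefore a guide to sensitivity, not the power of the final analysis.

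**Stronger readings.** A reader might infer that the maternal outcome is collected as yes/no answers. The yes/no rule is written for data use only. A reader might also infer that the trial is underpowered for this outcome, or that it will produce a false positive about half the time. The first needs an SD above about 14 points, which the document does not show. The second needs a staff-level test with ineffective matching, which it does not state.

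**Conclusion.** The definition and the sizing of maternal service utilisation do not match, and this is visible in the article's own text without any analysis plan. The 6 woredas per arm, 120 staff and 80% power are unsupported for this outcome because 85% of the variance they rest on does not apply to it.

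Unsupported does not mean low. Assuming one percentage per woreda, power for 25 points runs from above 99% at the printed k to 35% at an assumed SD of 25 points. The serious risk is conditional: if staff records are tested as independent, type I error is well above 5%, about 42–58% without effective matching and about 28–44% at an assumed within-pair correlation of 0.5. The matter should be settled before analysis, because the outcome is one of only two effectiveness outcomes.

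**What to change.** 1. In section 2.9, define the outcome as one value per woreda per period, computed from the district-office reports over the same calendar window before and after, and in the same way in both arms. Do not take it from staff interviews.
2. In section 2.12, state that this outcome is analysed on the 12 woreda values, with baseline adjustment and the matching taken into account, and not on staff records.
3. In section 2.5, replace the maternal row of the table with a woreda-level power statement across a range of between-woreda SDs, including the SD seen at baseline, using the degrees of freedom of the analysis chosen.

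The cost is a wording change plus extraction from reports that the team already acquires in all 12 districts; no new participants are needed. The downside is that the stated n for this outcome falls from 120 to 12, and the restated power may prove lower than 80% if woredas differ widely.

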### Data collection tools and procedures

2.10.

A pre-tested interviewer-administered structured questionnaire, based on the Performance of Routine Information System Management tools (version 3) (30) and adapted to the local context, has been used to improve data use in decision-making and utilization of maternal healthcare services through the DIPH approach in districts of the Gedeo Zone, southern Ethiopia, 2022. The questionnaire has two broad categories, namely, data use in decision-making and utilization of maternal healthcare service. It will be organized in an English version and then translated into local languages (Gedeuffa and Amharic) and finally retranslated into an English version to ensure consistency. The collection of baseline data has been carried out by the organized field teams. For end-line survey data collection, an independent team of four data collectors and one supervisor has been recruited for 1 month.

### Data quality assurance

2.11.

Before starting data collection, 5 days of training has been given to data collectors and the supervisor on the basic techniques of data collection and supervision. The supervisors have checked the accuracy, consistency, and completeness of the data daily. The questionnaire has been pre-tested by the same data collectors on 5% of the sample size (five health management staff) at one of the nearby district health offices with similar characteristics.

### Data management

2.12.

The data already collected have been routinely checked for completeness and consistency. After appropriate cleaning and coding, the data have been entered into EpiData version 4.6 and exported to SPSS version 23 software for analysis. Descriptive statistics have been generated and presented in narrative, figurative, and tabular forms. The *χ*^2^ and *t*-tests have been used in checking the statistical significance of the intervention and the difference in data use in decision-making and utilization of maternal healthcare services within and between groups. We have employed difference-in-differences estimates because the change may inherently happen over time. Therefore, a control group has captured this intrinsic temporal change without DIPH intervention and subtracted it from the change brought by the DIPH intervention to assess the net effect on key study outcomes. We have calculated the absolute differences in percentages from the baseline and the end line, then calculated the net effect by subtracting the absolute DIPH intervention difference from the control. A *P*-value of <0.05 and 95% confidence interval (CI) have been used to declare the significance of the intervention.

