**Methods:**

A two-arm parallel group, type II hybrid, cluster-randomized control trial design has been implemented to conduct the study between 1 September 2022 and 29 February 2024. Six woredas/districts have been assigned to the intervention arm and the other six to the control arm. Baseline and end-line data have been collected from 120 eligible health management staff (from both intervention arm and control arm). In the intervention arm, district health management staff have been given specialized training and continuous technical assistance as a package called the DIPH strategy by embedding it with the district's current decision-making platform such as Performance Review Team meetings. The DIPH strategy has mainly focused on five-step approaches such as situational assessment, stakeholder engagement, defining/setting priorities, planning, and follow-up. Health management staff in the control arm have performed their regular daily activities. The *χ*^2^ and *t*-tests have been used to check the effect of the intervention. In addition, difference-in-differences estimates have been calculated because the change may inherently occur over time. A *P*-value of <0.05 and a 95% confidence interval have been used to declare the significance of the intervention.

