### Selection of the population and allocation of the intervention

2.6.

The implementation research has been conducted in all woredas of the Gedeo Zone. Study woredas have been treated as clusters, with an equal number allocated to both intervention and non-intervention arms. Matched peer random allocation has been employed. To reduce subjective allocation, matching has been performed based on the performance level of the woredas (based on key indicators) and distance. The woredas have also been classified as urban and rural areas, and six intervention and six comparison arm woredas have been randomly selected in collaboration with the zonal health department. To avoid information contamination between the intervention and control arms, a buffer zone has been created based on the distance within the districts. Finally, all health management staff have been included in the selected woredas (Figure 1).

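### Woredas are randomised, but the named tests ignore the woreda, so P-values are too small and confidence intervals too narrow

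*Protocol article*

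**What the plan says.** **Design.** Section 2.2 calls the trial cluster-randomised. Section 2.6 says "Study woredas have been treated as clusters, with an equal number allocated to both intervention and non-intervention arms", and then "Matched peer random allocation has been employed" (read here as matched pairs), with matching on performance level and distance.

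**Sample size.** Section 2.5 uses a cluster formula, "assuming 80% power and at least 25 percentage point difference in the performance of data use and maternal healthcare services". It has ten staff per woreda and a between-woreda coefficient of variation of 0.096942 in both arms. The result is six woredas and 60 staff per arm.

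**Analysis.** Section 2.12 says that χ² and t "tests have been used in checking the statistical significance of the intervention and the difference in data use in decision-making", within and between groups. The Abstract says the same: these "tests have been used to check the effect of the intervention". For the net effect, section 2.12 adds "We have calculated the absolute differences in percentages from the baseline and the end line", followed by subtraction between arms. A P-value below 0.05 and a "95% confidence interval (CI) have been used to declare the significance of the intervention".

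No section names a woreda-level summary, a mixed model, generalised estimating equations, a cluster-robust variance or a pair term.

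**The concern.** A significance test has to use the variation between the units that were randomised. Here these are 12 woredas, not 120 people. Staff of one woreda office attend the same performance review meetings (section 2.6.1), work from the same data, and in the intervention arm are trained and supported together (section 2.8.3). Several components of the data-use score in section 2.9, such as programme coverage and evidence of data use, plausibly describe the office more than the individual. Their answers will be correlated.

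A χ² or t-test on 60 against 60 staff counts each answer as independent information. Its standard error is too small, and chance differences between woredas can be declared an intervention effect. Section 2.14 ties scale-up to a demonstration of effectiveness, so a false positive has consequences. This is not a detail left to a later analysis plan: the article names the tests that decide significance, and they conflict with its own design and sample-size formula.

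**Working it through.** **Inputs.** From section 2.5: m = 10 staff per woreda, six woredas per arm, π₀ = 0.50, π₁ = 0.75, k = 0.096942, 80% power, two-sided 5%. Intracluster correlations (ICC) above those implied by k are assumptions.

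**1. The plan's own figure.** The printed formula gives

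c = 1 + (1.96 + 0.8416)² × [0.25/10 + 0.1875/10 + 0.096942² × (0.25 + 0.5625)] / 0.25² = 1 + 7.849 × 0.05139 / 0.0625 = 7.45,

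which rounds up to 8 woredas per arm. The stated 6 does not follow. An individually randomised comparison of 50% with 75% needs 58 per arm and has 81.6% power at 60 per arm. So 60 per arm matches a calculation without clustering. This is a separate problem, but it bears on the cost of the fix.

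**2. ICC implied by k.** ICC = k²π²/[π(1−π)].
- At 50%: 0.009398 × 0.25/0.25 = 0.0094.
- At 75%: 0.009398 × 0.5625/0.1875 = 0.028.

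**3. Effect on the test.** The design effect is DE = 1 + 9 × ICC, and the normal-theory type I error of a nominal 5% test is 2·[1 − Φ(1.96/√DE)]. The last two columns come from 100,000 simulated null trials (6 + 6 woredas of 10, beta-binomial, 50%, matching that explains nothing).

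| ICC | DE | True SE / naive SE | Type I error, formula | χ², simulated | Paired woreda t-test, simulated |
|---|---|---|---|---|---|
| 0.0094 (from k) | 1.08 | 1.04 | 6.0% | 6.4% | 5.2% |
| 0.05 (assumed) | 1.45 | 1.20 | 10.4% | 11.4% | 5.3% |
| 0.10 (assumed) | 1.90 | 1.38 | 15.5% | 16.4% | 5.2% |
| 0.20 (assumed) | 2.80 | 1.67 | 24.1% | 25.7% | 5.3% |

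A separate simulation of 20,000 runs gave 6.6%, 11.4%, 16.6% and 25.6% for the χ² test. At the ICC of 0.028 implied at 75%, DE is 1.25 and the formula gives 8.0%.

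**4. Maternal service utilisation.** Section 2.9 defines this as a reported percentage. If one woreda figure is entered for each of ten staff, ICC = 1 and DE = 10, and the formula gives about 54%; a simulated t-test gives 58%. With within-office noise of 0.3, 0.5 and 1.0 times the between-woreda standard deviation, the simulated error is 55%, 53% and 42%.

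**5. Is the unit really staff?** Section 2.12 does not say so. However, section 2.3 interviews all eligible staff, the table in section 2.5 lists ten staff per woreda for both outcomes, section 2.9 grades data use as good or poor from 20 yes/no questions, and the Abstract counts 120 staff. For data use, χ² on good/poor is then a test on individuals.

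**The case against.** Four points can be made for the plan.

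- **The documented inflation is small.** The only between-woreda figure in the article gives about 6–8%, not 11–26%. This is true, and the higher values must be read as scenarios. But the article gives no source for k, and offices that share meetings and data could well be more alike than k implies.
- **Matching works the other way.** Ignoring effective pairs makes an unpaired test more conservative. If matching removes half the between-woreda variance, the simulated χ² error is 6.1%, 7.9%, 10.4% and 15.9% across the four ICCs in the table. If it removes 90%, it is about 5.5–5.8%. So the inflation comes from ignoring the woreda, not the pair. Nothing in the article shows that matching is that effective.
- **Difference-in-differences cancels stable woreda effects.** In a simulated naive test of that estimate (40,000 runs), with woreda effects assumed correlated 0.8 over time, the error is 5.6%, 6.6%, 6.9% and 8.7%. With correlation 1 it is 3.5–5.4%; with correlation 0 it is 6.8–26%. This stands for the net-effect estimate. But section 2.12 does not say what test goes with that estimate, and it does name χ² and t-tests between groups.
- **The unit is not stated.** A t-test on 12 woreda percentages of maternal service use would not have this fault. That is a possible reading for the second outcome, and the 42–58% figure is therefore conditional. It does not rescue the good/poor data-use outcome.

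**Conclusion.** The concern holds and must be fixed. The stated tests do not respect the randomised unit, so neither the 5% error rate nor the 95% coverage is assured. The existence of the fault does not depend on an assumed ICC; only its size does. For an endline χ² test with matching that explains nothing, the true error is about 6.0–6.6% at the protocol's k at 50% (about 8% at 75%) and about 11%, 16–17% and 26% at assumed ICCs of 0.05, 0.10 and 0.20. It is about 42–58% if a woreda figure is repeated by ten staff. Good matching or stable woreda effects would lower these values, but the article does not establish either. A woreda-level paired test stays at 5.2–5.3% in the simulations without effective matching and at 5.1–5.3% with it.

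**What to change.** Replace the χ² and t-test sentence in section 2.12, and its counterpart in the Abstract, with a cluster-level primary analysis:

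- Compute one endline summary per woreda for each outcome, adjusted for that woreda's baseline value. This keeps the aim of the difference-in-differences.
- Compare arms within the six matched pairs by a paired t-test on 5 degrees of freedom. Alternatively, use the exact within-pair permutation test: 2⁶ = 64 allocations, smallest two-sided P = 2/64 = 0.031.
- Take the 95% confidence interval from the same analysis.
- If staff-level data are modelled, use a mixed model with woreda and pair and a small-sample correction to the degrees of freedom.
- State the unit of analysis for each outcome, in particular whether maternal service utilisation is one value per woreda.
- If 1:1 pairs were not in fact formed (section 2.6 also mentions an urban/rural classification), use an unpaired woreda-level t-test on 10 degrees of freedom.

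This changes wording only. It needs the woreda of each questionnaire, but no new data and no linking of anonymous respondents. The cost is wider intervals and lower power. On the protocol's own inputs, six woredas per arm give about 68% (unpaired) or 58–65% (paired, from useless to perfect matching), against the stated 80%. That is the information the design holds, and the article should say so. The permutation test reaches 0.031 only when the observed allocation is the most extreme of the 64.

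### Before/after tests within an arm are among the tests for the intervention's significance, and the P<0.05 rule is not tied to the net effect, so a time trend shared by both arms could be declared a DIPH effect

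*Protocol article*

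**What the plan says.** Section 2.12 of the protocol article makes four statements that bear on this point.

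- χ² and t-tests are "used in checking the statistical significance of the intervention" and, in the same sentence, the "difference in data use in decision-making and utilization of maternal healthcare services within and between groups". No other test is named.
- The reason for the further estimate is explicit: "We have employed difference-in-differences estimates because the change may inherently happen over time". The control group is there to capture that change so that it can be taken out.
- The estimate is described as arithmetic. Percentage changes from baseline to end line are formed in each arm, and the authors then "calculated the net effect by subtracting the absolute DIPH intervention difference from the control". No standard error, model or test is named for the result.
- The section closes with a P-value below 0.05 and a 95% CI, which "have been used to declare the significance of the intervention". The contrast they belong to is not given.

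The Methods paragraph of the abstract has the same structure: the tests check the effect, and the difference-in-differences estimates are calculated in addition. The Introduction justifies a comparison group by the need to tell secular trends apart from a true intervention effect.

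**The concern.** A before/after test in the DIPH arm contains no control data. It responds to anything that moves the arm between rounds: DIPH, a background trend, or a change in how the answers are collected. The article expects change over time, and the rounds lie about 17 months apart (September 2022 to February 2024). The interviewers also change. The field teams collected the baseline data; then, "For end-line survey data collection, an independent team of four data collectors and one supervisor has been recruited". If that change applied alike in both arms, it is part of the shared shift and not a separate defect.

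The net effect is meant to be the answer, but the declaration of significance can rest on a contrast that the control group was added to replace. Section 2.14 makes scale-up depend on the intervention being shown effective, so it matters which P-value counts. The problem is separate from clustering and from having two outcomes: it would remain with woreda-level tests and a single outcome.

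**Working it through.** **Inputs from the article.** Section 2.5 gives a 50% baseline, 10 staff per woreda, 6 woredas (60 staff) per arm, and a coefficient of variation between woredas of k = 0.096942.

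**Assumptions not in the article.** DIPH has no effect. Both arms rise by the same 10, 15 or 20 points. The rounds are unlinked, so baseline and end-line responses are independent given the woreda. Section 2.13 says the questionnaire is anonymous, which makes this reasonable, but many of the same staff may answer twice.

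**The plan's own figure.** The printed formula in section 2.5 does not return 6 woredas per arm:

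c = 1 + 7.849 × [0.025 + 0.01875 + 0.009398 × (0.25 + 0.5625)] / 0.0625 = 1 + 6.45 = 7.45

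That is a separate matter. The check below uses the 6 × 10 per arm actually planned.

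**Step 1: within-DIPH-arm χ², by formula.** With n = 60 per round, p₀ = 0.50, end-line proportion p₁ and p̄ = (p₀ + p₁)/2:

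P(significant) ≈ Φ{ [ (p₁ − p₀) − 1.96 √(2p̄(1−p̄)/n) ] / √( [p₀(1−p₀) + p₁(1−p₁)]/n ) }

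- Rise to 60%: (0.10 − 0.1780)/0.0904 = −0.86, giving 19%.
- Rise to 65%: (0.15 − 0.1769)/0.0892 = −0.30, giving 38%.
- Rise to 70%: (0.20 − 0.1753)/0.0876 = 0.28, giving 61%.

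Because DIPH does nothing in this scenario, each figure is the chance of a false declaration if this test is the one used.

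**Step 2: simulation with woreda variation.** There were 40,000 trials per scenario. The woreda effects had SD 0.50 × 0.096942 = 0.048 and persisted over rounds, with 10 binomial responses per woreda per round. The last column is a t-test with 10 degrees of freedom on the woreda changes.

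| Shared rise | Within-DIPH χ² | End-line χ² between arms | Woreda-level test of difference in change |
|---|---|---|---|
| 10 points | about 20% | about 6% | about 5% |
| 15 points | 39–40% | about 6% | about 5% |
| 20 points | 62–63% | about 6% | about 5% |

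Ranges show the variation between repeat simulations.

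**Step 3: what drives the result.** The benchmark in the last column changes both the contrast and the unit of analysis. To separate the two, the difference-in-differences was also tested with a z-test that ignores clustering. It was significant in about 5–7% of trials whatever the rise. The inflation therefore comes from leaving out the control arm, not from the unit of analysis.

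**The case against.** The strongest defence is that the text can be read more kindly. The P-value and CI sentence comes directly after the description of the net effect and may be meant to apply to it. The sentence on χ² and t-tests gives them two objects, so the within-group tests may be intended as description alongside the test of the intervention. Both readings are possible. For that reason the fault is that no test is named for the net effect and the declaring contrast is left open. A reader might infer that the net effect will never be tested. The article does not say so, and an unseen analysis plan may specify the test.

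Leaving the standard error to an analysis plan would be no fault in itself. What stands is that the article does name within-group tests, in the sentence about the intervention's significance, and nothing afterwards excludes them from the declaration.

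A reader might also infer that an unadjusted end-line comparison between arms is invalid because it ignores baseline. That is not supported. Section 2.6 describes random allocation after matching, so the end-line contrast is a legitimate test of the intervention. Adjustment for baseline mainly gains precision and deals with chance imbalance. The excess over 5% in the end-line column comes from ignoring the woredas, not from the shared trend.

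Finally, the percentages depend on rises that the article does not state, and they cover a binary outcome only. Linked responses would change the within-arm figures but would not put control data into the test.

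**Conclusion.** The point holds as a badly fixed decision rule. Section 2.12 admits before/after tests among those for the intervention's significance, names no test or CI for the net effect, and does not say which contrast decides. An equal rise in both arms could therefore be declared a DIPH effect, against the reasoning in the Introduction and in section 2.12 itself.

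Under the assumptions listed, a declaration based on the within-arm χ² would be wrong in about 20%, 40% and 63% of trials for shared rises of 10, 15 and 20 points, against about 5% for a woreda-level test of the difference in change. A reader might take these as the trial's actual false-positive rates. They are not: they apply only if the within-arm test is used to declare an effect and a rise of that size occurs. That such a test cannot isolate DIPH depends on neither the size of the rise nor the linkage of the rounds.

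**What to change.** In section 2.12, and to match in the abstract:

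- State that significance is declared only from one between-arm effect, fixed before the end-line data are analysed. It may be the difference-in-differences or a baseline-adjusted end-line difference.
- Give that effect its own P-value and 95% CI, computed at woreda level and respecting the matched allocation.
- Report within-arm changes descriptively, and say that they are not used to declare an effect.
- Write the net effect as the DIPH change minus the control change. The printed subtraction runs the other way from the sentence before it.

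The cost is a few sentences of analysis text, with no change to design or data collection. The downside is that fewer results will reach P<0.05.
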